#### Work package 2: exclusion criteria

The exclusion criteria for work package 2 are: 1) deemed unsuitable to complete study (clinician advice); 2) currently enrolled in another clinical intervention trial; 3) receiving emergency inpatient care within 4 weeks of recruitment/assessment (patients admitted for routine procedures, e.g. dialysis access, will be eligible for inclusion); and 4) planned live donor kidney transplant during study period.

### Work package 1

#### Study protocol

Potential participants will be identified through a review of all patients attending haemodialysis sessions, currently available from electronic patient records (EPRs) and from clinicians in charge of each haemodialysis unit. Patient information leaflets (PILs) will be given to the patients in advance of a discussion with the researcher either by post or in person. Individuals will be approached at their usual dialysis unit appointment for discussion and potential recruitment to the study. Potential participants will be given the opportunity to reflect on the information given both verbally and within the PIL. No fixed time is specified for the length or timing of this prior interview as it will be dependent upon the patient’s understanding of their underlying disease and of the research project. It is important that non-English speaking patients are given full opportunity to be informed and recruited to the study, to accurately reflect the demographics of the haemodialysis population. In these instances, we will use any possibility to discuss the study with patients to aid participation and consent. This may include using family, friends, dialysis staff, or the investigator team who may be proficient in the patients preferred language (e.g. Urdu, Punjabi). Written consent will be received from each patient entering the study.

#### Baseline assessment

Prior to the patient being connected to the dialysis machine, the following assessments will take place: 1) timed walk over 4 m; 2) assessment of grip strength with a dynamometer; and 3) Montreal Cognitive Assessment (MoCA)

When the patient is dialysing, the following assessments will be performed: 1) quadriceps ultrasound assessment; 2) questionnaires will be given to participants in either paper or electronic format via a tablet device, according to patient preference, including the 3-level version of the EuroQol five dimensions (EQ-5D-3 L) and the Patient Health Questionnaire (PHQ)-9 (where a PHQ-9 score of 20 or over may indicate depression and a discussion will be held with the patient asking whether they would like a discussion with their nephrologist or a referral to the renal psychology service); and 3) a questionnaire related to each frailty instrument, demographic data, and social history (level of education, employment status, nature of employment, smoking, and alcohol history).

EPRs will be interrogated for data on comorbidities, dialysis parameters, previous transplantation, biochemical data, medication history, and social deprivation score.

The patient’s nephrologist will be invited to complete a Clinical Frail Scale for individual participants within 1 month of the baseline clinical assessment.

#### Data handling

Data collected throughout the study will be entered onto a study-specific database REDCap™ (Research Electronic Data Capture) [35] with secure storage and full oversight from information governance. Any paper records which form part of the source data for the study will be retained securely at site.

Patients will be consented for electronic data capture of clinical parameters (e.g. biochemical data) from University Hospitals Birmingham EPR at 1 month, 3 months, 1 year, 3 years, and 5 years post-recruitment (facilitated through informatics linkage utilising Hospital Patient Registration number). In addition, clinical outcomes (e.g. hospital admissions, medical events, surgical procedures, death, etc.) will be electronically captured from Hospital Episodes Statistics for the same time points (facilitated through informatics data linkage utilising National Health Service (NHS) numbers). This will allow long-term data capture of important clinical outcomes without direct patient involvement.

## Work package 2: plan of investigation

### Study protocol

The FITNESS protocol has been designed and reported in line with SPIRIT guidelines, with an attached SPIRIT flow diagram (see Fig. 2 later) and checklist (Additional file 1) [36].

#### Recruitment and consent

Potential participants will be identified through their previous participation in work package 1. Patients scored as “pre-frail” will randomly be selected to participate in work package 2. Patient information sheets will be given to the patients in advance of a discussion with the researcher either by post or in person. Individuals will be approached at their usual dialysis unit appointment for discussion and potential recruitment to the study. Potential participants will be given the opportunity to reflect on the information given both verbally and within the written information sheet. No fixed time is specified for the length or timing of this prior interview as it will be dependent upon the patient’s understanding of their underlying disease and of the research project. A certain level of English proficiency will be necessary to participate in the intervention, however it is important that non-native English speaking patients are given full opportunity to participate in this study and the same methods will be used as in work package 1 to facilitate this. Written consent will be received from each patient entering the study. A study patient identifier will be allocated and recorded on the study recruitment log.

Work package 1 patients who meet eligibility criteria will be randomly selected for participation in work package 2 using REDCap™ (in random permuted blocks within strata to balance numbers and characteristics). Participants who have subsequently been approached and given consent to participate in work package 2 will be randomised once more using REDCap™ (in random permuted blocks within strata to balance numbers and characteristics) into one of the following lifestyle intervention groups (*n* = 25 for each intervention group for a total of 50 participants). As part of the cm-RCT design, data from pre-frail work package 1 patients who were eligible but not selected for participation in work package 2 will provide a further comparator group for analysis. As an open-label study, neither participants nor researchers will be blinded to group allocation.

#### Active intervention group

This group will receive interventions designed to address frailty and will consist of dietitian referral for dietetic advice and physiotherapist referral for a graded exercise programme. The participants will receive this in addition to their usual haemodialysis standard of care. To reduce potential bias, neither the physiotherapist nor the dietitian will have regular input with haemodialysis patients as part of their job plan. Each patient will have five face-to-face appointments with the dietitian and physiotherapist (lasting 45–60 min) at baseline, week 6, week 12, week 18, and week 24. Brief telephone reviews will be conducted between appointments (approximately2–3 weeks after each face-to-face appointment) to review progress and provide additional support during the active intervention period. Some appointments may be substituted with telephone support if preferred by the patient. Patients will have their diet reviewed by a dietitian and healthy eating advice will be given based upon guidelines issued by the British Dietetic Association [37], which provide recommendations for minimum protein intake in dialysis patients. Patients will be advised to keep food and exercise diaries to monitor compliance with initiated changes and will be followed up by the research team prospectively (using face-to-face appointments and telephone reviews) to monitor progress and reinforce the advice (in addition to routine clinic visits). In addition, a graded exercise programme will be established by the physiotherapist to increase physical activity in line with both the patient’s stated goals at initial assessment and their deficits identified upon frailty scoring.

The dietitian and physiotherapist will be supported by a Senior Lecturer and Consultant in Addiction Psychiatry who has expertise in behavioural change therapy. The dietitian and physiotherapist will be trained with motivational interviewing skills and the following psychological tools will be utilised to support the active intervention.

Cognitive behavioural therapy (CBT) intervention incorporating NLM is simple to train and apply. We will utilise simple goal-setting techniques, combined with relapse prevention strategies, and a simple visual representation system for presenting CBT-type interventions. NLM is more effective than standard consultations for improving the therapeutic alliance, increasing focus on key issues during the session, and improving outcomes. There is also evidence of efficacy in patients with poor reading skills or working in a language other than their first language (important for our patient demographics) [31].

SBNT is an intervention that draws in members of the family, social network, and mutual self-help or peer support groups to help the patient set and achieve goals. It has been developed and tested by colleagues in Birmingham, with an evidence base in the context of liver transplantation [33]. A combination of these two techniques, together with motivational interviewing [38] by the dietitian and physiotherapist after appropriate training, will facilitate supportive psychosocial interventions to change lifestyle behaviour.

#### Passive control group

This group will receive their usual standard of care from their treating dialysis centre, including usual dietitian input. However, there will be no psychosocial intervention or focused exercise and dietary monitoring programme. Follow-up will be at routine clinic visits only, where lifestyle modification advice will be reinforced as per usual clinical practise. Physiotherapy may be offered to these patients as per standard referral guidelines but will not have the psychosocial underpinning of the intervention group.

Both groups will undergo a repeat frailty testing during the mid-point (3 months ± 2 weeks) and the end of study intervention (6 months ± 2 weeks) (see Figs. 1 and 2). The aim is to assess if there is any change in frailty status which will provide data to underpin a power calculation for a subsequent large-scale study. Additional pre-specified secondary outcomes will be collected as highlighted below in the protocol. Participants will also be invited to complete a series of questionnaires to ascertain the tolerability and suitability of the intervention trial, and to guide the delivery of the trial on a larger scale.

**Fig. 1 Fig1:**
[figure not shown]
Flowchart of participants in FITNESS work packages 1 and 2. As part of the cm-RCT methodology, all eligible participants will first be randomised for potential invitation to the study (*n* = 50). Potential recruits will then be approached for involvement in work package 2 and, after further valid consent, will then be randomised into active or passive groups

**Fig. 2 Fig2:**
[figure not shown]
Spirit figure for work package 2

### Study outcomes

#### Primary endpoint

The primary endpoint is the feasibility and tolerability of the clinical intervention study (recruitment rates, loss to follow-up, and study withdrawal).

#### Secondary endpoints

Secondary endpoints include: 1) refinement of the multi-disciplinary intervention based upon views from participants and stakeholders (from post-study questionnaires); 2) change in frailty status (based on Fried Frailty Phenotype, Clinical Frailty Scale); 3) difference in clinical and biochemical outcomes; 4) quality of life score (EQ-5D-3 L); 5) receipt of kidney transplant; 6) vascular access failure; and 7) long-term clinical outcomes (death, cardiac events, hospitalisation) to University Hospital Birmingham electronic patient records and Hospital Episode Statistics

### Data collection

#### Tissue collection

Blood samples will be taken from the 50 work package 2 participants, alongside 50 work package 1 participants each from the frail and non-frail groups. Plasma, serum, peripheral blood mononuclear cells (PBMCs) and whole blood will be stored for future immunophenotyping.

#### Electronic data capture

Electronic data capture will continue in work package 2 as previously described in work package 1.

#### Data monitoring and risk

There are no specific risks anticipated with this study. However, any study-related adverse events (AEs) will be documented and reported to the steering committee. Should a participant report any thoughts of deliberate self-harm or suicide, or complete a PHQ-9 score of over 20 during the study, a discussion will be held with the patient asking whether they would like a referral to the patient’s nephrologist or psychology services at the trust.

A serious adverse event (SAE) is defined by the Health Research Authority as an untoward occurrence that: 1) results in death; 2) is life-threatening; 3) requires hospitalisation or prolongation of existing hospitalisation; 4) results in persistent or significant disability or incapacity; 5) consists of a congenital abnormality or birth defect; and 6) is otherwise considered medically significant by the investigator.

An SAE occurring to a research participant will be reported to the Research Ethics Committee (REC) where in the opinion of the Chief Investigator the event was: 1) related (it resulted from the administration of any of the research procedures); and unexpected (the type of event is not listed in the protocol as an expected occurrence).

Any SAE will be reported to the REC within 15 days of the Chief Investigator becoming aware of the event. All other SAEs will need reporting as AEs on the case report form.

Exceptions to expedited reporting include hospitalisation for: 1) treatment which was elective or pre-planned, or for a pre-existing condition not associated with any deterioration in condition, e.g. pre-planned hip replacement operation which does not lead to further complications; and 2) treatment on an emergency, outpatient basis for an event not fulfilling any of the definitions of serious as given above and not resulting in hospital admission.

Patients will be asked if any adverse events have occurred when they attend for any trial-related procedure.

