## Background

Frailty is a state of low physiological reserve and multi-systemic dysregulation that leaves the individual susceptible to external stressors [1]. Sarcopenia, an age-related, involuntary loss of skeletal muscle mass and strength and/or function is often seen as part of the frailty syndrome [2, 3]. Immunosenescence is another component of frailty, characterised by age-related deterioration in immune function, and is thought to be modifiable through exercise [4]. Frailty is prevalent among patients receiving haemodialysis, ranging between 30% to as high as 78% dependent upon the diagnostic tool used, and is associated with significant adverse outcomes such as falls, hospitalisation, mortality, and loss of functional independence [5–17]. These studies were conducted in North American cohorts, primarily using the Fried Frailty Phenotype, and to date we have no information regarding the prevalence or outcomes associated with frailty in a UK cohort. Dialysis outcomes differ significantly between these populations [18], limiting the generalisability of US data to UK cohorts. Whilst there are a range of validated subjective and objective measurements for frailty, it is unclear which has the most utility to guide clinical practice.

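### For non-serious events, adverse events of any kind are asked about but only study-related ones are promised a record, so these harms cannot be compared by randomised arm

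*Protocol article*

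**What the plan says.** Everything on recording harms in work package 2 stands in the protocol article under *Data monitoring and risk*.

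- The general commitment is that "any study-related adverse events (AEs) will be documented and reported to the steering committee". It follows the statement "There are no specific risks anticipated with this study".
- Serious adverse events are defined by outcome, for example an event that "requires hospitalisation or prolongation of existing hospitalisation", with no condition on cause. Those that are related and unexpected go to the ethics committee. For the rest, "All other SAEs will need reporting as AEs on the case report form".
- Relatedness is judged in one stated place, the ethics committee route, "where in the opinion of the Chief Investigator the event was" related and unexpected. Related there means resulting from a research procedure.
- The section closes with: "Patients will be asked if any adverse events have occurred when they attend for any trial-related procedure".

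Elsewhere, *Recruitment and consent* states that "neither participants nor researchers will be blinded to group allocation". *Passive control group* gives controls usual care and has both arms repeat frailty testing at 3 and 6 months. *Active intervention group* describes a graded exercise programme, five face-to-face appointments and telephone reviews in between. *Secondary endpoints* and *Electronic data capture* provide for death, cardiac events and hospitalisation to be drawn from electronic records.

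**The concern.** Two sentences of one section do not fit together for a non-serious event. One has patients asked about anything that has happened. The other promises a record only of what is study-related. A member of staff who is told about an unrelated, non-serious event has no instruction to write it down.

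The filter also acts unequally on the arms. A control patient undergoes almost no research procedure to which a fall or strain could be attributed. The same event in a patient on the exercise programme may or may not be attributed, by people who know the allocation. In dialysis patients, some falls and injuries will happen anyway, and the cause of a single one is hard to settle. The concurrent control rate is what separates background from effect, and a relatedness filter applied before recording discards that rate. The loss matters because the trial is meant to inform whether a larger multi-centre trial is feasible and warranted.

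**Working it through.** The plan gives no adverse event figure to reproduce, so the main check is to follow each kind of event through the text.

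**1. Which events are certain to be recorded?**

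| Event | Active arm | Control arm | Source |
|---|---|---|---|
| Serious, any cause | Yes | Yes | *Data monitoring and risk* |
| Death, cardiac event, hospitalisation | Yes, electronically | Yes, electronically | *Secondary endpoints*; *Electronic data capture* |
| Non-serious, judged study-related | Yes | Yes, but can hardly arise | *Data monitoring and risk* |
| Non-serious, judged unrelated | Asked about; no commitment to record | Asked about; no commitment to record | *Data monitoring and risk* |

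Only the last two rows are a problem. A fall that leads to admission falls in the first row and is counted in either arm.

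**2. How can a control-arm event be study-related?** After baseline, the scheduled trial contacts of a control patient are the two repeat frailty tests and the questionnaires. A fall during a test could qualify; a fall at home could hardly do so. Active patients have in addition four post-baseline face-to-face appointments (weeks 6, 12, 18 and 24), telephone reviews and the exercise programme itself.

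**3. Does equal questioning cure this?** No. Both arms can be asked at 3 and 6 months, but the answer still meets the relatedness filter before it is recorded.

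**4. What could this do to the counts?** The article states no rate, so what follows rests on assumed rates. With n = 25 per arm, p the true proportion of patients with a non-serious event and s the share classed as study-related:

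expected number recorded = n × p × s

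| Assumed p | s = 1 | s = 0.5 | s = 0.25 | s = 0 |
|---|---|---|---|---|
| 10% | 2.5 | 1.25 | 0.625 | 0 |
| 20% | 5 | 2.5 | 1.25 | 0 |
| 40% | 10 | 5 | 2.5 | 0 |

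The chance that an arm records nothing is (1 − p × s)^25. At p = 20% this is 0.8^25 = 0.4% for s = 1, 0.9^25 = 7% for s = 0.5, 0.95^25 = 28% for s = 0.25, and 100% for s = 0. A usual-care arm sits near s = 0.

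If p is the same in both arms and s is about 0 in controls, the recorded difference is about p × s, with s taken from the active arm. At p = 20% it lies anywhere from 0 to 20 percentage points, although the true difference is zero. In the other direction, a real excess in the active arm disappears if s is near 0 there too.

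**The case against.** The strongest reply is that the sentence is a positive commitment tied to steering committee reporting. It does not contain the word *only*, and nothing says that other events go unrecorded. Patients are asked about any event, so the case report form may well take all of them, and form layout belongs to a full protocol that is not shown. This stands to a degree: the text does not forbid recording unrelated events. But the article does state a recording rule, the rule is limited by relatedness, and no sentence extends it to non-serious unrelated events. That is a badly worded rule, not a detail left out by condensation.

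Several stronger readings are tempting, and the document does not support them.

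- *The control arm has no harm count at all.* Not so: serious events are recorded irrespective of cause, and deaths and hospitalisations are captured in both arms.
- *The tolerability endpoint rests on attribution of events.* The primary endpoint is specified by recruitment, loss to follow-up and withdrawal, and participant questionnaires are added. None of these uses adverse event attribution.
- *The Background contradicts the statement that no specific risks are anticipated.* The Background says frailty is "associated with significant adverse outcomes such as falls, hospitalisation, mortality, and loss of functional independence". That describes what accompanies frailty, not a risk of the exercise programme.
- *An unblinded assessor is designated to filter these events.* No assessor is named for non-serious events; the Chief Investigator's judgement is stated for serious ones. What can be said is that no researcher is blinded.
- *The distortion will be large.* The upper end of the illustration needs every active-arm event to be called related. A team that anticipates no specific risks may lean the other way, which would leave both arms nearly empty.

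**Conclusion.** The point holds for non-serious events only. The section asks about any adverse event but commits to documenting study-related ones. With a usual-care control arm and no blinding, that order of steps leaves almost no non-serious control-arm events on record, so falls without admission and musculoskeletal injuries cannot be compared by randomised arm.

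The size is unknown: the article gives no event rate and no share judged related, and the tables above show only what assumed values would imply. The conclusion rests on reading the documentation sentence as the operative recording rule and on controls having little exposure to research procedures. It does not touch the primary endpoint or the comparison of serious events. It is an inexpensive improvement worth making, not a defect that undermines the trial.

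**What to change.** In *Data monitoring and risk*, replace the commitment on study-related events with one to document all adverse events, related or not, in both arms from randomisation to the 6-month assessment. Record relatedness afterwards as a field on the form. This also brings the sentence into line with the closing one on asking patients.

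At the 3- and 6-month assessments that both arms already attend, ask the same questions in both arms, including specific ones on falls and musculoskeletal injury. Base the between-arm comparison on these shared time points, because the active arm has more contacts at which events can come to light. Report counts by randomised arm to the steering committee.

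The cost is a change of wording, one case report form page, and more adverse event entries for 50 patients over 6 months. No extra visit is needed.
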